## Abstract

**Background:**

At birth, the majority of neonates born at <30 weeks of gestation require respiratory support to facilitate transition and ensure adequate gas exchange. Although the optimal approach to the initial respiratory management is uncertain, the American Academy of Pediatrics endorses noninvasive respiratory support with nasal continuous positive airway pressure (nCPAP) for premature neonates with respiratory insufficiency. Despite evidence for its use, nCPAP failure, requiring intubation and mechanical ventilation, is common. Recently, investigators have described a novel method to deliver bubble nCPAP, termed Seattle-PAP. While preclinical and pilot studies are encouraging regarding the potential value of Seattle-PAP, a large trial is needed to compare Seattle-PAP directly with the current standard of care for bubble nCPAP (Fisher & Paykel CPAP or FP-CPAP).

**Methods/design:**

We designed a multicenter, non-blinded, randomized controlled trial that will enroll 230 premature infants (22^0/7^ to 29^6/7^ weeks of gestation). Infants will be randomized to receive Seattle-PAP or FP-CPAP. The primary outcome is respiratory failure requiring intubation and mechanical ventilation. Secondary outcomes include measures of short- and long-term respiratory morbidity and cost-effectiveness.

**Discussion:**

This trial will assess whether Seattle-PAP is more efficacious and cost-effective than FP-CPAP in real-world practice among premature neonates.

**Trial registration:**

ClinicalTrials.gov, NCT03085329. Registered on 21 March 2017.

**Electronic supplementary material:**

The online version of this article (10.1186/s13063-018-3166-6) contains supplementary material, which is available to authorized users.

## Background

Neonates face significant challenges in the successful transition from fetal life [1, 2]. Aeration of liquid-filled lungs and the establishment of functional residual capacity are critical tasks in a newborn’s adaptation to the extrauterine environment. Beginning with their initial breath after birth, term infants clear fluid from their lungs and establish functional residual capacity to facilitate gas exchange [2]. In contrast, among many preterm neonates, surfactant deficiency, immature epithelial sodium channels, instability of the thorax, respiratory fatigue, and apnea contribute to respiratory insufficiency, often resulting in respiratory failure and the need for respiratory support [3–5]. Although the best approach to the initial respiratory management of these infants is uncertain, evidence that even brief exposures to tracheal intubation and mechanical ventilation cause lung injury have led to interest among health-care providers in the use of noninvasive respiratory support devices, primarily nasal continuous positive airway pressure (nCPAP) [6].

The American Academy of Pediatrics has endorsed the use of nCPAP among premature neonates with respiratory distress [7]. This recommendation is based on data indicating lower rates of bronchopulmonary dysplasia (BPD) in infants treated with nCPAP than are observed with more invasive modes of ventilatory support [8–10]. However, nCPAP failure, requiring intubation and mechanical ventilation in preterm infants, is common, with failure rates exceeding 50% in large clinical trials [8–10]. In developed countries, CPAP failure is associated with greater morbidity; in developing countries, CPAP failure is associated with greater mortality [11, 12].

More recently, bubble nCPAP has re-emerged as a potential strategy to address high nCPAP failure rates [13]. Although there are limited data, neonates on bubble nCPAP had a lower incidence of respiratory failure (tracheal intubation and mechanical ventilation) than did infants supported on ventilator-derived CPAP [12, 14]. Despite evidence that bubble nCPAP may be advantageous for preterm infants, the optimal delivery for newborns with respiratory distress is unknown. To address high failure rates associated with CPAP among preterm neonates, investigations of novel strategies to deliver more effective bubble nCPAP are warranted [15]. One potential strategy is the use of Seattle-PAP [12, 13, 16, 17].

In general, bubble nCPAP delivery systems consist of six primary components (Fig. 1): (1) sources of air, oxygen, and other breathing gases, (2) a blender to mix these gases together, (3) a gas heater and humidifier, (4) inspiratory and expiratory tubing (breathing circuit), (5) a patient interface (e.g., bi-nasal prongs or a nasal mask), and (6) a pressure generator (e.g., bubbler device). The design of the bubbler device can take many forms, but they generally comprise a tube with its distal end submerged in a body of water. The airway pressure provided by the system is determined largely by the depth of the distal end of the bubbler tube below the surface of the water (5 cm below surface = 5 cm H_2_O). In conventional bubble nCPAP systems, the bubbler tube points straight down (perpendicular to the surface of the water), which we define as 0°. With Seattle-PAP, the vertical section of the bubbler tube is connected to a horizontal section, which is connected to an upward sloping section, which we optimized at 135°.

**Fig. 1 Fig1:**
[figure not shown]
Schematic showing the primary components of a bubble nCPAP circuit. The differences in conventional and Seattle-PAP bubbler devices are shown. All other elements of the CPAP circuit are identical between the groups

Preclinical evidence demonstrated that this 135° modification provides fluctuations in airway pressures, including lower-frequency pressure oscillations than those created by conventional systems [17, 18]. Moreover, a recent study showed that prematurely born neonates (mean gestational age [GA] of 29 weeks) with minimal parenchymal lung disease exerted less effort in spontaneous breathing with a Seattle-PAP than a conventional bubble nCPAP (Fisher & Paykel CPAP or FP-CPAP) [13]. While the results of preliminary studies are encouraging, safety and efficacy data among smaller, more immature preterm infants are lacking.

If the Seattle-PAP arm proves superior to conventional bubble nCPAP, the likely benefits would be large, with clear applications in both the developed world and in low- and middle-income countries. However, to recommend Seattle-PAP over the current standard of care for bubble nCPAP (FP-CPAP), a large comparative trial is needed. Additionally, since respiratory failure is associated with higher daily costs related to more intensive monitoring and personnel requirements [19], Seattle-PAP may result in lower overall treatment costs if it prevents respiratory failure. Similarly, since infants failing CPAP stay in hospital longer than those successfully supported on CPAP, the total costs should be lower if use of Seattle-PAP is associated with a lower incidence of CPAP failure than FP-CPAP [20]. To estimate the cost-effectiveness of Seattle-PAP, a formal economic evaluation ancillary to the proposed randomized controlled trial (RCT) is necessary [21].

The present report describes the rationale and design for an ongoing RCT that aims to compare the effectiveness of Seattle-PAP versus conventional FP-CPAP in the prevention of respiratory failure of premature neonates born at 22^0/7^–29^6/7^ weeks’ GA. This study protocol was written in accordance with the Standard Protocol Items: Recommendations for Interventional Trials (SPIRIT) guidelines. The SPIRIT Checklist has been included in Additional file 1.

### Hypothesis

We are testing the hypothesis that premature neonates supported by Seattle-PAP will have lower rates of respiratory failure (need for tracheal intubation and mechanical ventilation) than will neonates supported with conventional bubble CPAP (FP-CPAP).

### Aims

The primary objective of this study is to compare the rates of respiratory failure from 72 h post-delivery to 32 weeks’ postmenstrual age in neonates born at 22^0/7^ to 29^6/7^ weeks’ GA who receive either Seattle-PAP or conventional bubble nCPAP (FP-CPAP).

## Methods/design

### Study settings

This is a multicenter non-blinded RCT in premature neonates born at 22^0/7^ to 29^6/7^ weeks’ GA. The trial is ongoing at five hospitals within the Neonatal Research Network (NRN) of the Nationwide Children’s Hospital (NCH): NCH Main Campus, Ohio State University Wexner Medical Center, OhioHealth Riverside Methodist Hospital, Mt. Carmel St. Ann’s Hospital, and OhioHealth Grant Medical Center. NCH is a Level IV referral facility covering Central Ohio and parts of West Virginia and Kentucky. All neonatal intensive care units (NICUs) in NCH-NRN routinely care for premature neonates with respiratory insufficiency, using FP-CPAP as a non-invasive respiratory support modality. Participating sites did not use Seattle-PAP prior to study commencement.

All participating sites administer an exogenous surfactant if the infant requires tracheal intubation for respiratory distress. One NICU (Mt. Carmel St. Ann’s Hospital) has some experience with less invasive surfactant administration, in which infants on bubble nCPAP are given a surfactant via thin catheters directly placed into the trachea while they are breathing spontaneously, thereby avoiding the need for intubation for surfactant administration [22]. All participating centers have 24-h on-site neonatal staff.

The Institutional Review Board (IRB) of NCH approved the trial (16–00678). The IRB at Mt. Carmel St. Ann’s Hospital granted separate approval for the trial (170817–2). Of note, prior to study commencement, the Seattle-PAP device received clearance from the U.S. Food and Drug Administration via the 510(k) pathway (K131502; 11 October 2013).

### Inclusion and exclusion criteria

The inclusion criteria are as follows:parental consent and/or legal guardian consent given to participate in this research studypreterm infants delivered at 22 to 30 weeks of completed gestation by best obstetrical estimateweight <1500 g at birthable to be weaned from mechanical ventilator support within 72 h of birth

The exclusion criteria are as follows:Infants with known major congenital cardiac (e.g., transposition of the great arteries), pulmonary (e.g., pulmonary and/or tracheal hypoplasia), or physiological (e.g., anencephaly, omphalocele, congenital diaphragmatic hernia) anomalies. For the purposes of this definition, common preterm cardiac issues such as patent ductus arteriosus and patent foramen ovale or atrial septal defect will not be grounds for exclusion.Infants with known genetic anomalies (e.g., trisomy 21).Infants born to mothers who are unable to give informed consent.

#### Recruitment

A member of the study team will approach parents of potentially eligible infants with threatened preterm delivery between 22^0/7^ and 29^6/7^ weeks’ GA to offer study participation and to obtain written informed consent. Consent will be obtained by team members who have been trained in obtaining consent for clinical trials and who are familiar with the trial protocol. Whenever possible, consent will be obtained by someone not directly involved in the clinical care of the infant. If it is not possible to obtain consent during the antenatal period, then as soon as possible following the birth, a member of the study team will approach the infant’s parents or legal guardians to obtain consent (up to 72 h post-delivery). Parents or guardians of infants who are not yet eligible but are likely to become eligible (e.g., infants requiring mechanical ventilation who are likely to transition from mechanical ventilation to bubble nCPAP prior to 72 h) will also be approached. Fig. 2 is the schedule of enrollment, interventions, and assessments. Recruitment began in March 2017.

**Fig. 2 Fig2:**
[figure not shown]
Schedule of enrollment, interventions, and assessments during the study

#### Randomization

Enrolled eligible infants are randomly assigned to one of two treatment arms (Seattle-PAP vs. FP-CPAP) (Fig. 3). The allocation sequence is generated using an online, computer-generated randomizer (https://sealedenvelope.com), with a block size of 6, stratified by GA (27–29^6/7^ and 22–27 weeks’ GA). We did not stratify by site, as the treatment of premature neonates is based on shared guidelines throughout the NCH-NRN [23]. Multiple gestations (twins or triplets) are assigned to the same treatment arm.

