#### Blinding

Blinding of the allocated treatment is not feasible, as the mode of respiratory support is apparent to health-care professionals and families. However, statisticians performing the data analyses will be blinded to group assignment. All enrolled neonates will be given clinical care according to established guidelines, including weaning, extubation, and reintubation [23]. Moreover, the primary outcome (respiratory failure, as defined below) is based on an objective set of criteria applied to both groups.

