#### Sample size

Using data from other recent large neonatal randomized trials with similar populations, including the SUPPORT trial and the COIN trial [9, 10], as well as contemporary data within the NCH-NRN, we estimate that the proportion of patients experiencing respiratory failure in the control arm (FP-CPAP) will be 50%. Based on preclinical work, we estimate the failure rate in the Seattle-PAP arm will be 30% [13, 17]. Accounting for two interim analyses, 200 neonates are needed with a two-tailed type I error rate of 0.05 and a power of 80% [25]. Multiples will be randomized as a set to the same study arm, requiring an inflation of the estimate by 1.12 to allow for the design effect due to clustering [26, 27]. Thus, the calculated sample size is 115 infants per treatment arm.

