### Study progress

The trial began recruiting in March 2017. It is expected that recruitment for the study will be completed in 2019.

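### A single disclosed block size of 6 in an open-label, still-recruiting trial lets someone who sees every allocation in a stratum foresee about a quarter of them (minor)

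*Protocol article*

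**What the plan says.** All references are to the protocol article.

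- **Randomization.** "The allocation sequence is generated using an online, computer-generated randomizer", "with a block size of 6". There are two gestational-age strata, and "We did not stratify by site". No other block size is named, and nothing says that sizes vary. A set of twins or triplets goes to one arm.
- **Sample size.** "Thus, the calculated sample size is 115 infants per treatment arm". Equal arms imply 1:1 allocation, so each block holds three places per arm.
- **Blinding.** "Blinding of the allocated treatment is not feasible", because staff and families can see which device is in use.
- **Study settings and Study progress.** Five hospitals are taking part and the trial is under way. "It is expected that recruitment for the study will be completed in 2019".
- **Inclusion and exclusion criteria; Recruitment.** An infant must be weanable from the ventilator within 72 h of birth. Parents are approached before delivery or up to 72 h after it, including parents of infants still ventilated but expected to qualify. A consent taker outside the clinical team is used where that can be arranged.
- **Training of clinical staff.** The principal investigator and study coordinator are on call to all centers.
- **Interim analysis.** Looks were taken after 25 and 110 infants, the second completed in January 2018.

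**The concern.** With a fixed, known block length, past allocations reveal future ones: once three infants in a block have gone to one arm, the rest of the block is settled. Three features make this relevant here. Past allocations can be seen. The block length is in print while infants are still being entered. And because the lists are not divided by site, there are only two sequences to follow.

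Foreknowledge does harm only if it can influence who enters and when. The 72 h window and the weaning criterion leave some room for that: a borderline infant could be entered sooner, later or not at all. If such choices followed the expected device, the arms would differ in prognosis at entry. Analysis as randomized does not correct this, and the planned primary comparison is an unadjusted Pearson chi-squared test.

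**Working it through.** The article gives no predictability figure, so there is none to reproduce. The check computes one.

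**Inputs.** Block of 6 (Randomization); 3 + 3 per block (from equal arms, Sample size); 230 infants in total (115 × 2); 110 enrolled at the second look (Interim analysis).

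**1. Allocations known with certainty, full view of a stratum.** There are C(6,3) = 20 equally likely blocks. The forced places are the final run of one arm:

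- one forced place: 12 of 20 = 0.60
- two: 6 of 20 = 0.30
- three: 2 of 20 = 0.10

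Mean = 1 × 0.60 + 2 × 0.30 + 3 × 0.10 = 1.5 places. 1.5 / 6 = **25%**, which agrees with the closed form 1/(m + 1) for m = 3. The sixth place of every block is always known.

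**2. Best-guess rate, full view.** The observer guesses the arm with more places left. The probability of being right, by place in the block, is 0.5, 0.6, 0.6, 0.7, 0.7 and 1.0. The sum is 4.1, and 4.1 / 6 = **68.3%**, against 50% by chance.

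**3. Partial view.** Simulation, assuming that each allocation in the stratum is seen independently with the stated probability and, generously, that the observer knows where blocks start:

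| Share of stratum list seen | Own allocations known with certainty |
|---|---|
| 20% (one of five sites, if sites were equal) | about 0.2% |
| 50% | about 3% |
| 80% | about 13% |
| 100% | 25% |

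**4. How many allocations.** 230 − 110 = 120 infants remained at most after the second look; 0.25 × 120 = **30**. This is a ceiling on the expected number. The article reports that look as already done, so it appeared later, and fewer may have remained by then. If a set of multiples takes one place on the list (an assumption), there are also fewer allocations than infants.

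**5. Effect of varying the block size.** Simulated lists, with an observer who sees everything and even knows the set of possible sizes:

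| Block sizes | Known with certainty | Best guess right |
|---|---|---|
| 6 only | 25% | 68% |
| 4 and 6 | about 5% | 69% |
| 4, 6 and 8 | about 2% | 68% |

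Varying sizes removes most of the certainty and hardly touches the guessing.

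**The case against.** The case for leaving the design alone is substantial.

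- **Few people have the full view.** Pooling the lists over five hospitals hides the sequence from bedside staff. This stands, and it limits the point to people who see every allocation in a stratum. A reader might infer that anyone aware of the block size can predict a quarter of allocations; the table for partial views shows otherwise.
- **The route from knowledge to action is not documented.** The article says that the principal investigator and coordinator can be reached by all centers. It does not say that they judge weaning or choose whom to approach. This stands as a limit: the opening exists, its use is not shown.
- **Safeguards narrow discretion.** Antenatal approach comes first, a non-treating consent taker is preferred, and respiratory care follows an algorithm with routine audits. These reduce the risk. The consent safeguard is conditional, so they do not remove it.
- **Delay often changes nothing.** It alters an allocation only if another infant in the stratum enters first. If 110 infants took 8 to 10 months, that is 11 to 14 a month. With an even split between strata and one place per infant, 0.54 to 0.69 entries per stratum are expected in 72 h (5.5 to 7 a month × 3 / 30.4 days), so the chance of at least one is 1 − exp(−0.54) to 1 − exp(−0.69), about 42% to 50%. This weakens the delay route but does not close it, and choosing not to approach a family remains possible.
- **The remedy leaves guessing untouched.** True, as the calculation shows. Removing near-certain knowledge is still a gain.

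A reader might also count unblinded intubation decisions against the block size. That is a question of outcome ascertainment and would be the same under any block scheme. Nor is the article's silence on how the list is held and released a fault, since that can sit in the full protocol. A concealed central list would in any case not prevent prediction from allocations already seen.

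**Conclusion.** The point holds in a limited form and is minor. Someone with a complete view of a stratum would know on average 25% of allocations in advance and guess 68% correctly; someone with a single-site view would rarely be certain. At most about 30 future allocations were affected.

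This rests on 1:1 allocation in complete blocks of 6, full tracking, and no enrolment beyond 110 infants at the time that counts. Relaxing either of the last two lowers the figure.

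Two stronger readings are not supported. One is that selection bias took place: nothing in the article shows that entry was steered. The other is that publication exposed 120 of 230 infants: that count starts at the second interim look, not at publication, and it counts infants rather than allocations.

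**What to change.** For allocations not yet made, regenerate each stratum's list with block sizes drawn at random, for example from 4, 6 and 8. Keep the sizes from recruiting staff, and publish them only after enrolment closes.

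The cost is a new list and a short amendment, which would go to the two review boards named under Study settings. The largest possible imbalance from a final incomplete block rises from 3 to 4 allocations per stratum (half of 6, half of 8). Treatment, outcomes, sample size and analysis are unchanged. The amendment should claim only what the change delivers: certain foreknowledge falls from 25% to about 2%, and the best-guess rate stays near 68%.

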**Fig. 3 Fig3:**
[figure not shown]
Study flow chart. bn-CPAP bubble nasal continuous positive airway pressure, CGA corrected gestational age

#### Intervention

The allocated treatment is applied immediately after randomization. Infants whose condition cannot be maintained with the assigned method of noninvasive respiratory support will be intubated and the originally assigned intervention resumed after extubation. In the NCH-NRN, bubble nCPAP is given through nasal prongs or a mask with an initial pressure of 5 to 6 cm H_2_O. As described above, the primary difference between the groups is the bubbler, which generates the pressure for the circuit (Fig. 1).

#### Blinding

Blinding of the allocated treatment is not feasible, as the mode of respiratory support is apparent to health-care professionals and families. However, statisticians performing the data analyses will be blinded to group assignment. All enrolled neonates will be given clinical care according to established guidelines, including weaning, extubation, and reintubation [23]. Moreover, the primary outcome (respiratory failure, as defined below) is based on an objective set of criteria applied to both groups.

#### Clinical and respiratory guidelines

Because the duration and type of respiratory support are critical end points, we have taken a number of steps to ensure that respiratory support is applied similarly to both groups: (1) NCH-NRN follows a respiratory algorithm for care (see Additional file 2: Figure S1) and (2) the thresholds for achieving the primary end point of respiratory failure are clearly defined (see below). In addition to standardized respiratory support, all aspects of neonatal management and treatment will be in accordance with local guidelines [23]. Internal audits to investigate maintenance and adherence to the guidelines are conducted on a routine basis.

*Treatment failure* is defined as any of the following:Tracheal intubation within 72 h for surfactant administration after initiation of bubble nCPAP and then not extubated by 72 h.Tracheal intubation of the infant or support with biphasic CPAP (SiPAP) in the NICU after 72 h and up to 32 weeks’ GA. As adjudicated by an independent party, tracheal intubation for non-respiratory issues after 72 h and up to 32 weeks’ GA (e.g., surgery for retinopathy of prematurity) will not be considered a treatment failure.The infant cannot sustain SpO_2_ of at least 90%, despite noninvasive respiratory support of up to and including 8 cm H_2_O bubble nCPAP, and FiO_2_ greater than 0.40 for more than 1 h.

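### Treatment failure counts an intubation before 72 h only if it was for surfactant, so some infants ventilated early for other respiratory reasons can be scored as successes

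*Protocol article*

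**What the plan says.** The Outcomes section makes treatment failure the primary outcome. Clinical and respiratory guidelines defines it by three components, any one of which is enough:

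- Component 1: "Tracheal intubation within 72 h for surfactant administration after initiation of bubble nCPAP and then not extubated by 72 h".
- Component 2: "Tracheal intubation of the infant or support with biphasic CPAP (SiPAP) in the NICU after 72 h and up to 32 weeks’ GA". An independent party decides whether an intubation is exempt, and the exemption is for "tracheal intubation for non-respiratory issues after 72 h and up to 32 weeks’ GA".
- Component 3: "The infant cannot sustain SpO_2_ of at least 90%, despite noninvasive respiratory support of up to and including 8 cm H_2_O bubble nCPAP", with FiO2 above 0.40 for longer than 1 h. No time window is attached.

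Several other sections bear on how these apply:

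- Under Intervention, "The allocated treatment is applied immediately after randomization". Infants who cannot be managed on the assigned device are intubated, and no surfactant condition is attached.
- The Discussion leaves enrolment open until 72 h of life. Recruitment includes approaching the parents of "infants requiring mechanical ventilation who are likely to transition from mechanical ventilation to bubble nCPAP prior to 72 h".
- Study settings says that every site gives surfactant when an infant is intubated for respiratory distress.
- The Hypothesis is about "lower rates of respiratory failure (need for tracheal intubation and mechanical ventilation", and the Abstract describes the primary outcome in the same terms. Neither mentions surfactant.
- The Aims section says the trial will "compare the rates of respiratory failure from 72 h post-delivery to 32 weeks" postmenstrual age.

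**The concern.** Between randomisation and 72 h of age an infant is already on the assigned device, and an intubation in that period can be a failure of that device. Component 1 counts such an intubation only when its purpose was surfactant. The Background names apnoea and respiratory fatigue alongside surfactant deficiency as causes of respiratory insufficiency, so other purposes are foreseeable.

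Two things are at stake. First, an infant who needed ventilation on the assigned device can enter the primary analysis as a success, contrary to the hypothesis being tested. Second, before 72 h the recorded reason for intubation can decide whether the event counts. Staff who know the allocation record that reason, and the protocol describes no independent review of it for that period. The Blinding section relies on the criteria being objective; this part of component 1 is not.

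**Working it through.** **Applying the three components.** Take an infant randomised before 72 h, intubated on the assigned device at about 40 h, and still ventilated at 72 h.

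1. Intubated for surfactant: component 1 is met. Failure.
2. Intubated for respiratory distress and given surfactant under site practice: probably component 1, although that component turns on the purpose of the intubation and not on whether surfactant was given.
3. Met the SpO2/FiO2 criterion first: component 3 is met whatever reason is recorded. Failure.
4. Intubated for apnoea or another respiratory reason without meeting component 3, later extubated, and neither reintubated for a respiratory reason nor put on SiPAP by 32 weeks: no component is plainly met. Scored a success.
5. As case 4, but reintubated for a respiratory reason or put on SiPAP after 72 h: component 2 is met. Failure.

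The gap is case 4.

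**Does component 2 already cover case 4?** It would if intubation there meant being intubated at any time after 72 h. But an infant not extubated by 72 h is, just after 72 h, still intubated. On that reading every component 1 failure would also be a component 2 failure, and component 1 would add nothing. The three-part structure makes sense only if component 2 means a new event.

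**The planned sample size.** Inputs from Sample size: 50% against 30%, two-sided alpha 0.05, power 80%, design effect 1.12.

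- n per arm = [1.960·√(2p̄(1−p̄)) + 0.8416·√(p1(1−p1) + p2(1−p2))]² / (p1−p2)², with p̄ = 0.40.
- [1.960 × 0.6928 + 0.8416 × 0.6782]² / 0.04 = 93 per arm, or 103 with continuity correction.
- 103 × 1.12 = 115.4, which agrees with the stated 115.

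**Illustrative effect on power.** Let a share s of true failures be missed equally in both arms. The values of s are assumptions. Effective n = 115/1.12 = 102.7 per arm, without continuity correction or allowance for the interim looks.

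- Power = Φ{[(p1−p2)·√n − 1.960·√(2p̄(1−p̄))] / √(p1(1−p1) + p2(1−p2))}.
- s = 0: 50% v 30%; [0.20 × 10.133 − 1.960 × 0.6928] / 0.6782 = 0.986; power 83.8%.
- s = 5%: 47.5% v 28.5%; power 80.5%.
- s = 10%: 45% v 27%; power 77.0%.
- s = 20%: 40% v 24%; power 69.3%.

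Unequal loss would also shift the estimate. With 115 infants per arm, each misclassified infant moves that arm's rate by 1/115 = 0.87 percentage points. If two points were lost in the control arm only (48% v 30%), power would be 75.7%. A loss confined to the Seattle-PAP arm would instead exaggerate the difference. The documents indicate neither direction.

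**The case against.** The strongest reply is that very few infants can reach case 4, and much of it stands. Because every site gives surfactant at intubation for respiratory distress, most early respiratory intubations will probably be read as component 1 events. Component 3 has no time window and catches hypoxaemic infants before 72 h. Component 2 catches later respiratory reintubation and SiPAP use. A reader might infer that every infant intubated early for a reason other than surfactant counts as a success; the definition does not support that. A reader might also take the recruitment of ventilated infants as showing that early reintubation without a further surfactant dose is expected. That section speaks only of infants likely to wean and says nothing about reintubation.

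The reply does not close the gap. Component 1 depends on purpose, apnoea is not plainly respiratory distress, and component 3 misses ventilatory failure without the oxygenation criterion.

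Three further objections have some force:

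- The shared respiratory algorithm and internal audits limit differences in practice between arms. They are not described as review of the recorded reason for an early intubation.
- Component 1 is settled by status at 72 h, so it is not far from the window in the Aims, and other sections mostly anchor 72 h to birth. These are matters of wording.
- Two interim analyses that included efficacy are complete, so changing the primary definition is not a trivial edit. This stands and shapes the fix.

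**Conclusion.** The point holds in a limited form. As written, the definition leaves a route by which an infant intubated on the assigned device before 72 h for a respiratory reason other than surfactant, and still ventilated at 72 h, is scored a success. It applies only if component 3 was not met and no later component 2 event occurs. This disagrees with the Abstract, the Hypothesis and the Intervention section, and it makes some primary-outcome classifications depend on an unadjudicated reason recorded in unblinded care.

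The conclusion rests on reading component 2 as a new event, which the structure of the definition favours but the text does not state. The size of the group cannot be derived from the documents and is probably small. A reader might take the 5% to 20% scenarios as an estimated loss of power; they are assumptions, and no loss is demonstrated. Nor is there evidence that labelling has differed between arms. The point merits correction because it decides who counts as a primary-outcome event and is cheap to settle.

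**What to change.** In the outcome definition, let component 1 count any post-randomisation intubation before 72 h for a respiratory reason, whatever the specific reason recorded, with the infant still intubated at 72 h. Extend the independent adjudication of non-respiratory intubations to those before 72 h. Reconcile Hypothesis, Aims and the definition of treatment failure so that they describe the same event and window, and state in component 1 that 72 h is counted from birth, as most other sections do.

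Make and date the change before the final analysis, through people without access to arm-level results, and record that it was made blind to them. If the primary definition is kept because two interim analyses are complete, pre-specify a sensitivity analysis of the primary outcome that counts these infants as failures.

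The cost is a short amendment, adjudication of a few early intubations, and re-derivation from the electronic medical records, the stated source of the clinical data. A few infants may change status, and a mid-trial change to the primary definition has to be reported openly. Clinical care is unaffected.
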